**Objective:**

The primary objective of this study is to assess the feasibility of conducting a parallel-group (1:1) randomized controlled trial (RCT) to evaluate a digital therapeutics (DTx) mindfulness-based intervention (MBI) in adolescents aged 12 to <18 years. The attention-matched comparator intervention (a math game also used in previous RCTs) will be delivered on the same DTx platform. Both groups will be provided with the standard of care guidelines. The secondary objective is to examine intervention trends for quality of life; resilience; self-efficacy; cognition such as attention, working memory, and executive functioning; symptom burden; and anxiety and depression scores at 4 weeks after concussion, which will inform a more definitive RCT. A subsample will be used to examine whether those randomized to the experimental intervention group have different brain-based imaging patterns compared with those randomized to the control group.

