#### Neuroimaging Procedures

A subset of 60 participants (30 from each group) will undergo a 45-minute MRI scan at <72 hours and 4 weeks after injury. During the day 1 phone call, participants who have consented to the MRI component of the study will complete the MRI screener and schedule their MRI appointment.

Each scanning session will be approximately 1 hour and will include a high-resolution structural scan, arterial spin labeling, rs-fMRI, and magnetic proton spectroscopy (Table 4).

**Table 4 table4:** Magnetic resonance imaging acquisition.

Image type	Sequence name	Total time (minutes:seconds)	Resolution (mm×mm×mm)	Slices, n	FOV^a^ (mm)	TR^b^ (milliseconds)	TE^c^ (milliseconds)	Other
High-resolution anatomical	MEMPRAGE	5:48	1.0**×**1.0**×**1.0	192	256	2500	1.69, 3.55, 5.41, and 7.27	Flip angle=7; inversion time=1050 milliseconds; phase FOV=100%
rs-fMRI^d^	—^e^	12:08	3.0**×**3.0**×**3.0	40	204	2160	25	Flip angle=70; acceleration factor=2; 334 volumes
ASL^f^	3D ASL (GRACE)	5:37	1.8**×**1.8**×**5.0	34	230	4600	15.56	Perfusion mode=Flow-sensitive Alternating Inversion Recovery-QII; bolus duration=700 milliseconds; inversion time=860 milliseconds, 1060 milliseconds, 1260 milliseconds, 1460 milliseconds, 1660 milliseconds, 1860 milliseconds, 2060 milliseconds, 2260 milliseconds, 2460 milliseconds, 2660 milliseconds, 2860 milliseconds, 3060 milliseconds; average=1
ASL	Calibration image (M0)	0:54	1.8**×**1.8**×**5.0	34	230	7500	15.92	Perfusion mode=Flow-sensitive Alternating Inversion Recovery-QII; bolus duration=700; inversion time=7000 milliseconds; average=1
MRS^g^	PRESS	4:38	40**×**20**×**15	—	—	2000	30	Average=128
MRS	MEGAPRESS	4:36 (×2)	40**×**20**×**15	—	—	2000	68	Average=64

^a^FOV: field of view.

^b^TR: repetition time.

^c^TE: echo time.

^d^rs-fMRI: resting-state functional magnetic resonance imaging.

^e^Not available.

^f^ASL: arterial spin labeling.

^g^MRS: magnetic resonance spectroscopy.

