#### Neuroimaging Component: Nested Study

To acquire preliminary data on the association between the interventions and MRI metrics, per-protocol analyses will be conducted. A multivariable linear regression will be performed for each neuroimaging outcome, with age, sex, and handedness (for rs-fMRI) as covariates. If the groups differ at baseline on potentially confounding variables, such as attention-deficit or hyperactivity disorder, anxiety, medication, prior concussion, physical activity, and puberty, these variables will also be entered as covariates in the models. Per-protocol analyses will include only those participants who have adhered to the intervention.

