##### Sample Size for the Nested Neuroimaging Component

As per Desmond and Glover [90], a liberal threshold of α=.05 requires 24 participants (12 per group) to achieve an 80% power for the single-voxel level for typical activations. To control the error rate when conducting multiple comparisons, it is suggested that the number of participants should be doubled to maintain this level of power. On the basis of our Pediatric Concussion Assessment of Rest and Exertion and MRI study, of the 89 participants with concussion who provided consent, 13 were lost to follow-up, 3 had incidental findings, and 5 had excessive motion [91]. Considering a 20% attrition, a total sample size of 60 participants (30 per group) will be recruited.

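### The only stated imaging analysis keeps adherers alone, so it does not compare the groups as randomised, and the sample of 60 makes no allowance for the participants it excludes

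*Protocol article*

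**What the plan says.** The Objective in the Abstract sets the imaging question as "whether those randomized to the experimental intervention group have different brain-based imaging patterns compared with those randomized to the control group". The Discussion goes further and asks whether the programme induces measurable effects on the brain.

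Under Neuroimaging Component: Nested Study, the analysis is per-protocol: "Per-protocol analyses will include only those participants who have adhered to the intervention". Each imaging outcome gets a linear regression "with age, sex, and handedness (for rs-fMRI) as covariates". Further variables such as anxiety, medication and prior concussion enter if the groups differ on them at baseline. No as-randomised imaging analysis is stated.

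Under Sample Size for the Nested Neuroimaging Component, "a liberal threshold of α=.05 requires 24 participants (12 per group) to achieve an 80% power". For multiple comparisons, "it is suggested that the number of participants should be doubled to maintain this level of power". Of 89 consenting participants in the team's earlier MRI study, "13 were lost to follow-up, 3 had incidental findings, and 5 had excessive motion". The section concludes: "Considering a 20% attrition, a total sample size of 60 participants (30 per group) will be recruited".

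Table 2 sets the adherence thresholds: green above 70%, red below 50%.

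**The concern.** Randomisation makes the two arms comparable at the start. Keeping only adherers gives that up, because adherence is behaviour that follows allocation. The tasks also differ. One arm works through meditation, psychoeducation and journaling, with some practices of up to 15 minutes. The other plays a tile game that closes after 10 minutes a day. Those who keep up with the first need not resemble those who keep up with the second in symptoms, motivation or mood, and age, sex and handedness cannot repair that.

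The size of the imaging subset is also at odds with its analysis set. The allowance covers attrition only, and none of the earlier-study losses cited in its support is an exclusion for non-adherence. The analysed number would therefore fall below the one the calculation was built to deliver. An imaging difference or its absence could then be carried into the case for the efficacy trial on a selected and smaller comparison than the plan suggests.

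**Working it through.** **Inputs.** From the imaging sample-size section: 24 participants (12 per group) for 80% power at alpha .05, a doubling for multiple comparisons, 20% attrition, and 60 recruited. From the same section: 13, 3 and 5 losses among 89. From Table 2: adherence limits of 70% and 50%. Adherence of 80% and 90% is added to show the range, because the article gives no expected rate for the imaging subset.

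**The plan's own figure.** 24 × 2 = 48 evaluable, and 48 / (1 − 0.20) = 60. The stated size is reproduced. The 48 is implied, not printed.

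**Losses in the earlier study.** (13 + 3 + 5) / 89 = 21/89 = 23.6%. Applied to this trial, 60 × (1 − 0.236) = 45.8, about 46 before any adherence filter.

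**Adherers-only number.** Analysed = 60 × retention × adherence among those retained. Adherence is applied after dropout because the feasibility sample-size section inflates its adherence number separately for about 20% loss.

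| Adherence | After 20% attrition | After 23.6% loss |
|---|---|---|
| 100% | 48 | 45.8 |
| 90% | 43.2 | 41.3 |
| 80% | 38.4 | 36.7 |
| 70% | 33.6 | 32.1 |
| 50% | 24.0 | 22.9 |

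If adherence is instead counted over all 60 and every dropout is a non-adherer, 70% leaves 60 × 0.7 = 42, still below 48.

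**Number needed to keep 48 adherers.** N = 48 / (0.8 × adherence). At 70% this is 85.7, so 86. At 80% it is 75, and at 90% it is 66.7, so 67. The first two exceed the whole trial of 70.

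**Illustrative power, on the plan's own premises.** The article gives no effect size, so I work back from its statements, assuming a two-sided two-sample t-test.

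1. 80% power with 12 per group at alpha .05 implies a standardised difference of about 1.20.
2. The doubling is meant to keep 80% power under multiplicity control. With that difference and 24 per group, 80% power corresponds to an alpha of about 0.002.
3. At that difference and alpha, 17 per group (about 34 in all, 70% adherence) gives about 56%, and 12 per group (50% adherence) about 32%.

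**The case against.** The strongest reply is about purpose. The imaging section says it seeks preliminary data, imaging is one of eight secondary objectives, and progression rests on five feasibility criteria, none of them imaging. Looking at adherers is a recognised exploratory choice when the question is mechanism. The conditional confounder adjustment also offsets part of the selection. All of this stands and lowers the severity. It does not supply the missing as-randomised comparison that the objective describes.

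Three stronger readings are tempting but not supported.

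- A reader might take 34 as the most that can be analysed. It is the count at the lower edge of the green zone, and better adherence gives more.
- A reader might infer that the first scan is ignored. Participants "will undergo a 45-minute MRI scan at <72 hours and 4 weeks after injury", and the first-scan value is not among the listed covariates. But the article does not define the imaging outcome. A change score would use the first scan, and the full protocol or analysis plan may settle it.
- A reader might set 80% power at 24 per group with alpha still at .05 and compute the loss from there. That conflicts with the section's own premise that 12 per group already suffices at that alpha. At alpha .05, with the implied difference of 1.20, 17 per group would still have about 92%. The loss of power appears only under the stricter threshold that the doubling implies.

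The gap between 23.6% and 20% is small: 46 instead of 48. The article reports the earlier losses openly.

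**Conclusion.** The point holds and should be fixed. The one stated imaging analysis conditions on adherence and so does not answer a question about those randomised to each group. That follows from the article's own choice of analysis set, not from something left to another document. How far selection differs between arms cannot be known in advance. That it may differ is enough to give up the protection of randomisation.

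The size of 60 delivers the implied 48 only if attrition is 20% and every retained participant adheres. At 70% adherence the shortfall is 14 or 15 participants, and at 90% about 5. The counts assume that adherence is measured among those retained. The power figures of about 56% and 32% also rest on the assumed t-test and the back-calculated difference and alpha, so they illustrate the scale and are not forecasts. The feasibility conclusions are unaffected.

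**What to change.** 1. Make the main imaging analysis all randomised participants with usable scans, in their allocated arm. State that scan completion is itself determined after randomisation, and report it by arm.
2. Define the outcome as the week-4 metric and model it on arm, first-scan value, age and sex, plus handedness for resting-state fMRI.
3. Keep the adherers-only analysis, with its additional confounder adjustment, as a labelled sensitivity analysis.
4. Restate the expected analysable number as about 46 to 48 as randomised, and give the smaller adherers-only number with the adherence rate assumed.

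The cost is wording. The article says data analysis has not been conducted, so no scan or recruitment target need change. The as-randomised estimate may be diluted by non-adherers, which the sensitivity analysis would help to show. One caution on the covariate: the first MRI is booked during the call at which participants are randomised, and the app starts the day after enrollment, so some first scans may follow a few days of use. The plan should say so and report the interval by arm.

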#### Statistical Power

##### Feasibility Objective

The sample size calculations were informed on recommendations for feasibility trials using the *traffic light* system [50,89]. The significance cutoff points for each criterion, with green lower and red upper limits, were determined. Using Table 1 from the study by Lewis et al [50], to meet the individual >90% power requirements for each of the five criteria we would need the following: (1) for eligibility, the number of participants to be screened is 46; (2) for recruitment, the number of participants to be randomized is 54; (3) for adherence, the required number of participants to evaluate adherence is 55; (4) for credibility, the required number of participants is 55; and (5) for retention, the required number of participants is 34. To determine the overall sample size for the whole study, we based our decision on the criterion that requires the largest numbers (ie, adherence, n=55). Considering an approximately 20% rate of loss to follow-up and withdrawals, the required sample size for the adherence criteria is 70. We expect that 40% of the participants screened will be eligible and there will be a 50% recruitment uptake. Given these numbers, 350 children are expected to be screened: 350=[(1/0.4)×(1/0.5×70)]. Assuming that 70 of the 350 screened participants are randomized, criteria 1, 2, 3, 4, and 5 will have statistical powers of 100%, 99.9%, 95.8%, 95.8%, and 98.7%, respectively. This means that the null hypotheses can be rejected with a collective power of 90.5% if the alternative hypotheses (for acceptable feasibility outcomes) are true in each case.

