### Intervention Description

#### Experimental Group Description: MBI Training

To be delivered via the *AmDTx* platform (Figure 2), the targeted DTx MBI training consists of a 4- to 8-week custom-made program (containing 8-modules) for adolescents with concussion, including setting intentions and check-ins on mood and stress, audio-recorded lectures, guided meditations such as focused attention exercises, and journaling events (Table 1). Each standardized psychoeducation or meditation practice will be unlocked as the participant progresses through the MBI program. Participants will be encouraged to participate in the DTx MBI activities for approximately 10 minutes every day, for a minimum of 4 days a week, over the 4- to-8-week period. Those who choose to end their therapy on the fourth week will be immediately directed to module 8 *Reviewing the program and how to maintain practice*. Those who choose to continue for an additional 4 weeks will move on to modules 5 through 8. The curriculum is based on previously validated *AmDTx* MBI app protocols [27,43] and team expertise in youth MBI ([name], [name], MC, and [name]) and was peer reviewed by experts in the field and parent engagement leaders ([name], [name], and [name]). The intervention was piloted on 10 pediatric participants with concussion, and their feedback was integrated into the MBI and protocol [36]. We will track *meaningful* in-app use time, defined as the time spent engaging in meditation, psychoeducation, self-monitoring, and self-reflection, with a minimum threshold of 3 minutes per day. Any use time <3 minutes will not be counted toward the total weekly minutes spent using the *DTx.*

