### Measures and Outcomes

#### Primary Outcomes

The prespecified thresholds (criteria for success), as outlined in Table 2 for the feasibility, are based on established benchmarks of previous feasibility trials [47,48] and our previous experience in recruiting pediatric patients with concussion from an ED [49]. We will use the *traffic light* system to determine whether proceeding to a full-scale trial is appropriate [50]. Progression can take place without any changes (green zone), with correctable adjustments (amber zone), or not occur because of issues that cannot be readily addressed (red zone). The decision to progress to a full-scale trial will be contingent on the criterion with the least favorable performance [50].

Table 3 provides an overview of all outcome measures collected and their specific end points.

**Table 2 table2:** The criteria for success for progression to a full-scale efficacy trial.

Feasibility outcomes	Green zone (go)	Amber zone (amend)	Red zone (stop)
Eligibility	>40% of participants screened are eligible	20%-40% of participants screened are eligible	<20% of participants screened are eligible
Recruitment	>50% of eligible participants will be randomized [49]	30%-50% of eligible participants will be randomized	<30% of eligible participants will be randomized
Adherence	>70% of participants complete the minimum requirements, that is, approximately 10 minutes of activity 4 times a week	>50% of participants complete the minimum requirements, that is, approximately 10 minutes of activity 4 times a week	<50% of participants complete the minimum requirements, that is, approximately 10 minutes of activity 4 times a week
Credibility^a^	>70% of participants have score above the scale midpoint	>50% of participant have a score above the scale midpoint	<50% of participants have a score above the scale midpoint
Retention	>75% participants complete the follow-up assessment [49]	50%-75% participants complete the follow-up assessment	<50% participants complete the follow-up assessment

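### The stated feasibility powers mix denominators (70 for adherence and credibility, 55 for retention), so no consistent reading reproduces the printed powers and their 90.5% product

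*Protocol article*

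**What the plan says.** The Feasibility Objective paragraph (Protocol article, Statistical Power) asks for more than 90% power on each of five criteria. It gives a requirement of 55 for adherence, 55 for credibility and 34 for retention. Adherence drives the total: "Considering an approximately 20% rate of loss to follow-up and withdrawals, the required sample size for the adherence criteria is 70". With 350 screened and 70 randomised, it then reports that "criteria 1, 2, 3, 4, and 5 will have statistical powers of 100%, 99.9%, 95.8%, 95.8%, and 98.7%, respectively", and concludes that the "null hypotheses can be rejected with a collective power of 90.5" per cent. It does not say which number of participants stands behind each power.

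Table 2 sets the limits. For adherence, green is ">70% of participants complete the minimum requirements"; for credibility, ">70% of participants have score above the scale midpoint". Retention is the share of participants who complete the follow-up assessment, with limits of 50% and 75%. The intervention description says the app will track meaningful "in-app use time, defined as the time spent engaging in meditation, psychoeducation, self-monitoring, and self-reflection".

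**The concern.** The increase from 55 to 70 makes sense only if some randomised participants cannot be evaluated for adherence; on the plan's allowance about 55 or 56 can. The quoted power for adherence is nevertheless the power with all 70. Retention is the one criterion whose denominator must include those who are lost, yet its quoted power is the one for 55. Loss is therefore ignored where the paragraph allows for it, and applied where it cannot apply.

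The collective figure matters because Table 2 is read by its weakest criterion: the decision to progress follows the least favourable result. A reader will take 90.5% as the chance that a truly feasible trial passes all five tests.

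**Working it through.** **Inputs.** Red and green limits from Table 2:
- eligibility 0.20 and 0.40 (green: ">40% of participants screened are eligible")
- recruitment 0.30 and 0.50 (amber: "30%-50% of eligible participants will be randomized")
- adherence 0.50 and 0.70
- credibility 0.50 and 0.70
- retention 0.50 and 0.75

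Numbers from the Feasibility Objective: 350 screened; 350 × 0.4 = 140 eligible; 140 × 0.5 = 70 randomised; about 20% loss, so 70 × 0.8 = 56 evaluable (55 is the stated requirement, and 55/0.8 = 68.75, rounded up to 70). The article gives no alpha for these tests; one-sided 5% is inferred from the fit below.

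**Formula.** One-sample test of a proportion, normal approximation with continuity correction:

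power = Φ{ [(p1 − p0) − 1/(2n) − 1.645·√(p0(1−p0)/n)] / √(p1(1−p1)/n) }

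It gives required numbers of 47, 54, 55, 55 and 35, against the stated 46, 54, 55, 55 and 34.

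**Step 1: reproduce the printed powers.**
- Eligibility, n=350: 100.0%.
- Recruitment, n=140: 99.92% (stated 99.9%).
- Adherence and credibility, n=70: (0.200 − 0.0071 − 0.0983)/0.0548 = 1.726, so 95.8%, as stated.
- Retention, n=55: (0.250 − 0.0091 − 0.1109)/0.0584 = 2.227, so 98.7%, as stated.
- Product of the printed values: 1 × 0.999 × 0.958² × 0.987 = 0.905, as stated.

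Other conventions do not fit. Without the continuity correction the two key powers are 96.8% and 99.1%; with one-sided 2.5% they are 91.7% and 96.9%.

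**Step 2: exchange the denominators.**
- Adherence or credibility, n=55: (0.200 − 0.0091 − 0.1109)/0.0618 = 1.295, so 90.2%. At n=56: 90.8% (0.9075).
- Retention, n=70: (0.250 − 0.0071 − 0.0983)/0.0518 = 2.793, so 99.7%.

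**Step 3: collective power under each consistent reading** (eligibility 1.000, recruitment 0.9992, retention 0.9974 at n=70 throughout).

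| Adherence n | Credibility n | Product | Collective power |
|---|---|---|---|
| 70 | 70 | 0.9992 × 0.9579² × 0.9974 | 91.4% |
| one of the two at 55, the other at 70 | | 0.9992 × 0.9023 × 0.9579 × 0.9974 | 86.1% |
| one of the two at 56, the other at 70 | | 0.9992 × 0.9075 × 0.9579 × 0.9974 | 86.6% |
| 55 | 55 | 0.9992 × 0.9023² × 0.9974 | 81.1% |
| 56 | 56 | 0.9992 × 0.9075² × 0.9974 | 82.1% |

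**Sensitivity to the formula.** With exact binomial tests the last two rows become 76.9% and 82.9%, and the first becomes 90.3%. The ordering holds, but the decimals should not be pressed.

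**The case against.** The strongest reply is that nothing in the article restricts adherence to those who stay. Table 2 speaks simply of participants, app use is tracked, and the powers are stated for 70 randomised. On that reading 95.8% for adherence is right. The 20% allowance is attached only to adherence, and credibility is asked at week 1, when less will be missing. With adherence and retention on 70, credibility on 66 responders gives a collective 90.4% and on 63 gives 89.5%, so the printed total lies within the plausible range.

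Most of this stands. It rules out presenting 81% as the power of the design: that figure needs the full loss on both adherence and credibility, which the article does not state. It does not rescue the paragraph. If all 70 count for adherence, the stated reason for raising 55 to 70 falls away; and on any reading 98.7% is not the power for retention on 70. Agreement of the total near 66 responders is a coincidence of offsetting terms, because the component powers still differ from those printed.

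A reader might also infer that adherence will be reported among completers and so be biased upwards; for example, 70% of the 80% retained is 56% of all randomised if no dropout adheres. The article states no completers-only rule, so this is a risk to close off and not an error in the plan. Nor does the point show the trial to be too small. The size was set on individual power, which by the plan's formula is still 90.2% at n=55 (exact binomial: 87.9% at 55, 91.3% at 56), and collective power enters no decision rule.

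**Conclusion.** The point holds as an inconsistency in the stated powers. The printed set requires 70 for adherence and credibility and 55 for retention, which neither the loss allowance nor the definition of retention supports. Retention power should read 99.7%. Collective power is about 91%, 86-87% or 81-82% according to whether the loss applies to neither, one or both of adherence and credibility. The chance that a truly feasible trial misses at least one criterion is then roughly 9%, 13-14% or 18-19%, against the 9.5% implied.

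This rests on three assumptions: one-sided 5%, inferred because it reproduces the printed powers; true rates exactly at the green limits; and independence of the criteria, which the plan's own product also assumes. The sample size of 70 stands.

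**What to change.** In the Feasibility Objective, give the denominator beside each power and use the same denominators in Table 2.

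- Retention: all 70 randomised, power 99.7%.
- Adherence: preferably all 70, from app logs, with withdrawals and non-users counted as non-adherent; power 95.8%. This also closes the route to an inflated adherence rate.
- Credibility: the number expected to answer the week-1 questionnaire, with its power.
- Collective power to match: about 86-87% if credibility has 55-56 responders; about 91% if it is nearly complete at week 1; about 81-82% if adherence, too, is assessed only in those retained.
- If adherence is taken on all 70, reword the reason for going from 55 to 70, since loss no longer explains it. Naming the alpha used would let readers check the figures.

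The cost is wording and possibly a less favourable stated power. No extra participants or data are needed.

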^a^Treatment credibility and expectancy will be assessed using the Credibility and Expectancy Questionnaire [51]. It is a 6-item questionnaire, scored using a Likert scale ranging from 1 to 9. The treatment will be considered credible (questions 1-3) if the participants scored above the midpoint. Furthermore, credibility and expectancy will be assessed to rule out the possibility of differential credibility as an explanation for the differences in therapy outcomes between the experimental and control groups. The credibility and expectancy of the intervention will be assessed at 1 week after enrollment.

**Table 3 table3:** Measures organized by domain, source of data, and assessment occasion.

Measures				Source or reporter		Time to complete (minutes)		CHEO ED^a^		360cc^b^		Daily^c^		Day 1 (CHEO)		Day 1 (360cc)		72-hours		Day 7		Day 14		Week 3		Week 4		Week 8

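### The 90.5% collective power mixes denominators: credibility is powered on all 70 randomised with no questionnaire missing, while retention is powered on about 55

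*Protocol article*

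**What the plan says.** The protocol article, under Statistical Power, Feasibility Objective, sizes the trial on five progression criteria, each with its own power requirement of more than 90%. For one of them it says: "4) for credibility, the required number of participants is 55". Adherence has the same requirement, and 55 is the largest of the five. The paragraph then allows for attrition: "Considering an approximately 20% rate of loss to follow-up and withdrawals, the required sample size for the adherence criteria is 70". On the assumption that 70 of 350 screened adolescents are randomised, it reports that "criteria 1, 2, 3, 4, and 5 will have statistical powers of 100%, 99.9%, 95.8%, 95.8%, and 98.7%, respectively" and concludes that "the null hypotheses can be rejected with a collective power of 90.5"% if every criterion is truly acceptable.

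Table 2 (Measures and Outcomes, Primary Outcomes) sets the credibility limits. Green is ">70% of participants have score above the scale midpoint" and red is "<50% of participants have a score above the scale midpoint". For retention the corresponding limits are 75% and 50% of participants completing follow-up. Footnote a of Table 2 says that credibility comes from a questionnaire and fixes its timing: "The credibility and expectancy of the intervention will be assessed at 1 week after enrollment".

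**The concern.** The step from 55 to 70 exists because some participants are expected to supply no data. A credibility score needs a returned questionnaire, so credibility is a criterion for which attrition can shrink the number analysed. A power computed on all 70 treats the participants added to cover loss as if none were lost. Retention is the reverse case: a participant who drops out is still observed, as not retained, so its denominator is everyone randomised. If one power uses the number before loss and the other the number after, and the choice is the wrong way round for both, their product describes no single scenario.

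The product matters because the plan lets the worst-performing criterion govern progression. Collective power is then the figure that tells a reader how likely a truly feasible trial is to pass all five tests.

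**Working it through.** **Inputs.** From Table 2: credibility and adherence 0.50 (red limit) against 0.70 (green limit); retention 0.50 against 0.75; eligibility 0.20 against 0.40; recruitment 0.30 against 0.50. From the Feasibility Objective paragraph: 350 screened, 70 randomised, about 20% loss. At 40% eligibility, 350 × 0.4 = 140 are eligible. Loss of 20% leaves 70 × 0.8 = 56. The article gives no numerical alpha; one-sided 0.05 is assumed because it reproduces the plan's figures.

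**Formula.** One-sample test of a proportion, normal approximation with continuity correction:

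power = Φ( [p1 − p0 − 1/(2n) − 1.645·√(p0(1−p0)/n)] / √(p1(1−p1)/n) )

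**Check on the required sizes.** The sample-size formula for this test at 90% power gives 46.2, 53.5, 54.6, 54.6 and 34.2, against the plan's 46, 54, 55, 55 and 34. A two-sided version gives 66.3 for credibility, so the one-sided assumption is well supported.

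**Reproducing the stated powers.**

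- Eligibility, n = 350: 100%. Recruitment, n = 140: 99.9%. Both agree.
- Credibility and adherence, n = 70: (0.20 − 0.0071 − 0.0983)/0.0548 = 1.726, so power is 95.8%. This agrees, and only with 70 analysed.
- Retention, n = 55: (0.25 − 0.0091 − 0.1109)/0.0584 = 2.227, so power is 98.7%. This agrees.
- Retention, n = 70: (0.25 − 0.0071 − 0.0983)/0.0518 = 2.793, so power is 99.7%. This does not agree.
- Product of the stated powers: 1 × 0.999 × 0.958 × 0.958 × 0.987 = 0.905. This agrees.

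So the printed 90.5% combines credibility at 70 with retention at about 55. (At n = 56 the same formula gives 98.8% for retention and an exact binomial test gives 98.7%; either way the figure belongs to the number after loss.)

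**Credibility with fewer questionnaires.** At n = 56: (0.20 − 0.0089 − 0.1099)/0.0612 = 1.326, so power is 90.7%. An exact binomial test gives 91.3% there, and 95.2% at n = 70.

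**Collective power on consistent denominators.** Retention and adherence are at 70, and products are taken from unrounded powers:

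| Week-1 questionnaires returned | Credibility power | Collective power |
|---|---|---|
| 70 (none missing) | 95.8% | 91.4% |
| 66 (about 5% missing) | 94.7% | 90.4% |
| 63 (10% missing) | 93.7% | 89.5% |
| 56 (20% missing) | 90.7% | 86.6% |

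For the last row: 0.9992 × 0.9579 × 0.9075 × 0.9974 = 0.866.

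**Adherence.** Keeping it at 70 supposes that app use is logged for everyone and that those who stop count as non-adherent. If the 20% loss also removes participants from the adherence denominator, the product is 0.9992 × 0.9075 × 0.9075 × 0.9974 = 0.821, about 82%.

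**The case against.** The strongest defence is that no stated target is missed. The plan requires more than 90% power for each criterion separately. Credibility still has 90.7% at 56, and no target is set for collective power. The inflation from 55 to 70 does its job. This stands.

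Second, the allowance "Considering an approximately 20% rate of loss to follow-up and withdrawals" is an overall rate that the plan attaches to adherence. Credibility is measured at week 1, when loss may well be smaller, and coaches remind participants to complete surveys. This also stands: the 20% row is an unfavourable case, not the plan's own forecast of questionnaire return.

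Third, a missing questionnaire could be counted as not credible, which would keep the denominator at 70. The article states no such rule, and the full protocol or analysis plan may. Under that rule, though, non-response would lower the expected proportion below 70%, so 95.8% would still assume complete return.

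Fourth, progression depends on which zone the point estimate falls in, and amber still allows progression with changes. If true credibility is 70%, the exact binomial chance of an estimate at or below 50% is about 0.04% at n = 70 and 0.13% at n = 56. Missing questionnaires would therefore hardly ever push credibility into red.

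A reader might infer that collective power falls to 85.7% at the plan's loss rate, or that even 5% missing questionnaires takes it below 90%. Both results come from correcting credibility while leaving retention at its stated 98.7% (0.999 × 0.958 × 0.9075 × 0.987 = 0.857; with 66 questionnaires, 0.999 × 0.958 × 0.947 × 0.987 = 0.895). Once retention is also put on its proper denominator, 5% missing gives 90.4% and 20% missing gives 86.6%.

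**Conclusion.** The concern holds as a fault in reporting. The 95.8% for credibility takes no loss, the 98.7% for retention uses a number after loss where all 70 belong, and the 90.5% combines the two. The errors run in opposite directions and partly cancel. Consistent collective power is 91.4% with complete questionnaire return, stays just above 90% with about 5% missing, and is 89.5% at 10% and 86.6% at 20% missing. It is about 82% if the 20% loss also shrinks the adherence denominator.

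The documents do not support the inference that the trial is too small or misses a power requirement: the only requirement stated is for individual criteria, and credibility meets it at 56.

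These figures rest on an inferred one-sided alpha of 0.05 with continuity correction, on the plan's own practice of multiplying the five powers as if independent, and on assumed week-1 return rates, since none is given.

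**What to change.** In the Feasibility Objective paragraph, state the denominator for each criterion and recompute:

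- Retention on all 70 randomised: about 99.7%.
- Credibility on the expected number of returned week-1 questionnaires, as a range: 95.8% at 70, 94.7% at 66, 93.7% at 63, 90.7% at 56.
- Adherence on 70, with a sentence saying that participants who stop using the app count as non-adherent. If that is not intended, use the reduced number.
- Collective power as the matching range: about 91.4%, 90.4%, 89.5% and 86.6%, or about 82% if adherence also loses 20%.

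State the alpha and its sidedness beside these figures. Say whether a missing credibility questionnaire is left out of the denominator or counted as a failure, and report the number missing by arm.

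The cost is the rewording of one paragraph. No extra participants, data or procedures are needed. The collective figure becomes a range, part of which lies below the single value now printed.
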